#### Analysis of primary aims

The primary analysis for aim 1A will be according to the intention-to-treat (ITT) principle. All live born infants and all stillborn infants born at ≥22 weeks gestation or weighing at least 500 g will be included, with infants classified according to the treatment assignment made at the time of the mother’s enrolment. For aim 1B, the primary analysis will be according to modified ITT, beginning from the first assigned dose. Sensitivity analyses of the two aims will be modified as-treated. If a mother or infant receives at least one study dose of azithromycin, they will be classified as being in the corresponding azithromycin-receiving study arm. Percent lost to follow-up will be compared across treatment arms for each intervention. Among those lost to follow up, baseline characteristics will be compared to assess whether loss is differential by intervention or by treatment arm. In the 2×2 factorial design, the primary analyses will fit a Cox proportional hazards regression model with two indicator variables for the two interventions, with censoring at the earliest of documented refusal for further participation, death, last study contact or recorded source of vital status, or attainment of 12 months of age. The study is not powered to detect a statistical interaction effect between the two interventions, but if it is important (p<0.05 or ratio of HRs >1. 5 or <0.67), results for all four study arms will also be reported. For primary aim 1A, the analysis timeline will be calculated from delivery, with stillbirths assigned day 0.1. For primary aim 1B, the timeline will start at the receipt of the first infant dose. For a measure of overall public health impact on infant mortality, a supplementary analysis will be done with the timeline starting at the live birth.

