Ideally, pregnant participants are dosed in the second and third trimesters, but to accommodate individual variations in ANC timing, the first dose is administered at the enrolment ANC visit and the second dose at the next routine ANC visit or at delivery, whichever occurs sooner. The delivery dose is given during labour when possible but may be administered within 24 hours after delivery regardless of whether the infant is stillborn or liveborn. Infants are dosed when they present to a study facility to receive their first and third doses of pentavalent vaccine. Infants must be at least 6 weeks of age to receive the first dose of study medication.

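### The modified as-treated rule counts azithromycin first received at Penta-3 back to the start of aim 1B follow-up, which favours azithromycin slightly whenever bottles are mixed up

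*Protocol article*

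**What the plan says.** All of this is in the protocol article, mostly under Analysis of primary aims.

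- **Primary analyses.** Aim 1A is intention-to-treat, by the arm allotted when the mother joined the trial. Aim 1B uses a variant that counts from dosing: "the primary analysis will be according to modified ITT, beginning from the first assigned dose".
- **As-treated analyses.** These are the supporting ones: "Sensitivity analyses of the two aims will be modified as-treated". The arm then follows the drug: anyone who "receives at least one study dose of azithromycin, they will be classified as being in the corresponding azithromycin-receiving study arm". The rule is worded for a mother or an infant.
- **Clocks.** The aim 1B clock runs from dosing: "For primary aim 1B, the timeline will start at the receipt of the first infant dose". The aim 1A clock runs from birth: "the analysis timeline will be calculated from delivery, with stillbirths assigned day 0.1".
- **Model.** The Cox model described for the primary analyses has two indicators, one per intervention. No time-varying exposure is mentioned.
- **Dose timing.** Infant doses are given at Penta-1 and Penta-3, at about 6 and 14 weeks of age (Study design, objectives and hypotheses). The first maternal dose is given at the enrolment antenatal visit, and the delivery dose "may be administered within 24 hours after delivery regardless of whether the infant is stillborn or liveborn" (Intervention).

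**The concern.** In a Cox model with a fixed exposure indicator, exposure has to be known when follow-up starts. In aim 1B this rule lets a dose given about 8 weeks later decide it. Two kinds of infant are affected, both with placebo at the first dose and azithromycin at Penta-3:

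- a placebo-assigned infant given the wrong bottle at Penta-3;
- an azithromycin-assigned infant given the wrong bottle at Penta-1 and the right one at Penta-3.

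Either child counts as azithromycin if it reaches Penta-3 and receives that dose, and as placebo if it dies first. The early deaths stay with placebo, while the survivors' early time at risk moves to azithromycin. The comparison therefore leans towards benefit even with no drug effect.

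Aim 1A has a separate hazard. If the same rule sets the infant indicator in a two-indicator model timed from delivery, no stillbirth and no infant who dies before Penta-1 can be coded as having received infant azithromycin.

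This is the only sensitivity analysis that the article names for the coprimary aims. It departs from assignment only through participants who did not receive the drug assigned, and those are the infants whom the rule can misplace.

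**Working it through.** **The plan's own figure for scale.** The article gives no figure for the as-treated rule. The nearest is Table 3, revised, aim 1B: 9/1000, with detectable reductions at 80% power of 24.7% (49 600) and 22.3% (with 12 000 infant-only infants, 61 600 in all). I assume two-sided alpha 0.05.

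Total N = 2 × (1.960 + 0.842)² × [p₁(1−p₁) + p₂(1−p₂)] / (p₁−p₂)²

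- 24.7%: p₂ = 0.009 × 0.753 = 0.006777, N ≈ 49 700.
- 22.3%: p₂ = 0.009 × 0.777 = 0.006993, N ≈ 61 800.

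Both reproduce. At 61 600 and 9/1000 there are about 554 deaths, so the standard error of the log hazard ratio is about 2/√554 = 0.085.

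**Aim 1B, true effect nil.** From the article: p = 0.009. Assumed: wrong-bottle rate e per dose, share s = 0.3 to 0.6 of post-dose deaths before Penta-3, and Penta-3 attendance a = 0.85.

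Take one unit of infants assigned to each arm. Wrong bottles at the first dose swap e each way, so each as-treated group starts with one unit. Later movers from placebo to azithromycin come from both routes:

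- placebo-assigned: (1−e) × a × e
- azithromycin-assigned: e × a × (1−e)

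Together k = 2e(1−e)a, and all of them have survived to Penta-3. Early deaths stay at p·s in each group. Late deaths become p(1−s)(1+k) in azithromycin and p(1−s)(1−k) in placebo. Group sizes become 1 ± k(1−ps). Since ps is at most 0.0054,

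ratio ≈ {[1 + (1−s)k] / (1+k)} ÷ {[1 − (1−s)k] / (1−k)}

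Example: e = 0.01 gives k = 2 × 0.01 × 0.99 × 0.85 = 0.0168. With s = 0.6, (1.0067/1.0168) ÷ (0.9933/0.9832) = 0.980.

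| Wrong bottles per dose | k | Both routes, s = 0.3 / 0.6 | Placebo-assigned route only (k = ea), s = 0.3 / 0.6 |
|---|---|---|---|
| 0 | 0 | 1.000 / 1.000 | 1.000 / 1.000 |
| 1% | 0.017 | 0.990 / 0.980 | 0.995 / 0.990 |
| 2% | 0.033 | 0.980 / 0.961 | 0.990 / 0.980 |
| 5% | 0.081 | 0.953 / 0.908 | 0.975 / 0.951 |

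The size depends on counting both routes; the first alone gives about half the shift. A Cox simulation of the first route only (30% of deaths before Penta-3, full attendance) gave as-treated to intention-to-treat ratios of 0.996 at 1% misdosing and 0.967 at 5%, and exactly 1 with none.

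In standard errors, the two-route shift is 0.12–0.24 at 1% and 0.57–1.13 at 5%.

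**Aim 1A, infant indicator set as-treated, true effect nil.** Table 3 gives 74/1000 for the composite and 9/1000 after 6 weeks. About 74 − 9 = 65 per 1000 events come before the first infant dose (approximate, because one rate is per birth and the other per live birth). About 935 per 1000 then remain, half of them assigned infant azithromycin. Let a share g of survivors be dosed (assumed 0.75 to 0.95).

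- g = 0.75: azithromycin 3.4 deaths in 350.6; all others 70.6 in 649.4; ratio 0.089.
- g = 0.95: azithromycin 4.3 deaths in 444.1; all others 69.7 in 555.9; ratio 0.077.

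In a Cox simulation with all survivors dosed, the infant hazard ratio was 0.067. The maternal hazard ratio was 1.00 for a true 1.0 and 0.90 for a true 0.9, so it was not disturbed.

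**The case against.** The strongest reply is that correct dosing leaves nothing to bias. The first maternal dose precedes the aim 1A clock, and the aim 1B clock starts at the first infant dose. Anyone dosed as assigned has the arm-defining dose by time zero and keeps that arm if death comes before the next dose. Under Randomisation and masking, labels are barcoded and each bottle carries a bin letter, so errors may be rare. The misdosing rate is an assumption. The analysis is only a sensitivity analysis, described briefly in a condensed article, and exposure coding is often left to the analysis plan.

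Most of this stands and limits the size of the point. The last part does not dispose of it, because the article states the classification rule rather than leaving it open.

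A reader might also infer more than the documents support:

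- **That arm in general depends on surviving to later doses, or that the primary results are biased.** Only misdosed infants are affected, and the primary analyses do not use this rule.
- **That the rule is wholly one-sided, so a wrong placebo dose moves nobody.** An azithromycin-assigned infant given placebo at Penta-1 who dies before Penta-3 moves to placebo. The two-route figures depend on this.
- **That a maternal dose after a stillbirth adds to the bias towards azithromycin.** Moving that stillbirth into the azithromycin arm adds an event there, which works against azithromycin. On the aim 1A clock, any such delay is at most about a day.
- **That aim 1A is distorted to a ratio near 0.08.** That needs the two-indicator model, described for the primary analyses, to be carried into the sensitivity analysis with both indicators as-treated. It then concerns the infant coefficient, which is not the aim 1A estimand.
- **That the sensitivity analysis cannot be interpreted.** At a 1% error rate the shift is at most about a quarter of a standard error.

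**Conclusion.** The point holds in a narrow form. For aim 1B the rule is not tied to time zero, and where it acts it favours azithromycin. The bias grows with the bottle-error rate: none without errors, 2% or less at 1% per dose, and about 5% to 9% at 5%, against a detectable reduction of 22.3%. These sizes rest on assumed error rates, attendance and timing of deaths. For aim 1A the problem is conditional on how the infant indicator is coded. It is a modest defect in a supporting analysis, worth correcting because the remedy is specific and almost free.

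**What to change.** Replace the classification sentence with a rule fixed by the start of follow-up: as-treated status is the drug received at the first maternal dose for aim 1A and at the first infant dose for aim 1B. Alternatively, enter later doses as time-varying exposure. Add that in any model timed from birth the infant indicator stays as randomised.

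The cost is one sentence and a few lines of code. The trade-off is that infants first exposed at Penta-3 count as azithromycin only from that dose, or not at all. Reporting the observed number of wrong-bottle doses beside the analysis would show whether the issue had any practical weight.

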#### Interim analysis

There is one prespecified formal interim analysis for efficacy planned for the maternal intervention, to take place when half of the expected number of stillbirths and infant deaths have occurred. This analysis will be run with an interim type I error of 0.007, which is expected to require a maternal intervention relative efficacy of at least 13%. Due to the complexity of this 2×2 factorial design, if this level was reached, the DSMB would consider all available data, and decide whether to stop randomisation to one or both interventions.

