## Methods and analysis

### Study design, objectives and hypotheses

Sauver avec l’Azithromycine en Traitant les Femmes Enceintes et les Enfants (SANTE) is an individually randomised, placebo-controlled, double-masked trial. Using a 2×2 factorial design with four treatment arms, SANTE will simultaneously assess coprimary aim 1A: whether azithromycin administered at routine antenatal care (ANC) visits (second and/or third trimester) and at delivery reduces a composite outcome of stillbirth and infant mortality, and coprimary aim 1B: whether azithromycin administered to infants concurrently with the first and third doses of pentavalent vaccine (Penta-1 and Penta-3) reduces mortality from the time of the first dose through 6–12 months of life. We will enrol 49 600 pregnant participants who will be randomised to receive 2 g azithromycin or placebo as a single oral dose twice during pregnancy and at delivery, for up to three total doses. Their infants will be randomised to receive 20 mg/kg azithromycin or placebo as a single oral dose at their routine Penta-1 and Penta-3 vaccination visits (figure 1). According to the national routine immunisation schedule, these vaccination visits occur at approximately 6 and 14 weeks of age, respectively. Infants are followed through at least 6 months and up to 12 months of age. To increase statistical power for aim 1B, a separate cohort of 12 000 infants, the infant-only cohort, is recruited at the Penta-1 visit. Infants enrolled in the infant-only cohort are randomised, dosed and followed in the same manner as those born to pregnant participants. Participant enrolment commenced in September 2020 and is expected to be complete by April 2023.

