### Statistical considerations

#### Sample size and power

The original power calculations for the primary aims were based on anticipated stillbirth and infant mortality rates in the Sikasso/Koutiala regions estimated from published data at the time the trial was being designed (table 3). Analysable endpoints were expected for at least 85% of enrolled participants. After the trial was initiated, observed stillbirth and infant mortality rates in the study population, pooled across blinded treatment arms, were used to update the sample size targets from 33 600 to 49 600 in the mother–infant cohort and from 8500 to 12 000 in the infant-only cohort (online supplemental appendix table 4). The resulting sample sizes are large, as infant mortality even in Mali is relatively rare, resulting in somewhat small absolute differences. For example, for Aim1B, with a baseline IMR of 9/1000, a 24.7% relative reduction means detecting an absolute reduction of less than 3 deaths per 1000.

**Table 3 T3:** Sample size assumptions and minimum detectable relative reductions for the coprimary aims

	Original	Revised
Target sample size, mother–infant cohort	33 600*	49 600

Aim 1A. Effect of intervention on composite outcome of stillbirths and infant deaths from birth to 12 months		
Baseline combined stillbirth and infant mortality rate	105/1000†	74/1000†
Minimum detectable relative mortality reduction, comparing azithromycin to placebo treatment arms		
80% power	9.5%	8.7%
90% power	10.9%	10.1%

Aim 1B. Effect of intervention on infant deaths from first dose (approx. 6 weeks) to 12 months		
Infant mortality rate	28/1000‡	9/1000‡
Minimum detectable relative mortality reduction, comparing azithromycin to placebo treatment arms		
80% power	18.6%	24.7%
90% power	21.4%	28.3%
With addition of infants from the infant-only cohort§		
80% power	16.6%	22.3%
90% power	19.1%	25.6%

*In the original sample size calculation, 15% anticipated loss to follow-up (LTFU) meant that 28 560 infants were expected to have analysable endpoints.

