†Original assumed composite baseline stillbirth and infant mortality was 105 deaths per 1000 births, calculated from 33 stillbirths/1000 births^55^ and 74.8 infant deaths per 1000 live births (Sikasso data, Mali 2012 Demographic and Health Survey [DHS] report^56^), assuming that 6–11 months mortality data are available for 90% of infants and subtracting stillbirths from the live birth denominator. Revised observed composite stillbirth and infant mortality rate in the study population is 74 deaths per 1000 births.

‡Original baseline infant mortality rate after 6 weeks of age was 28 per 1000 live births (Sikasso data, 2012 Mali DHS report) assuming that 6–11 months mortality data are available for 90% of infants; revised infant mortality rate after 6 weeks of age was updated to 9 deaths per 1000 live births based on observed mortality in the study population.

§Original target sample size for infant-only cohort was 8500, assuming 7650 analysable (10% LTFU); revised target sample size 12 000.

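### The 13% efficacy expected at the interim look and the revised detectable reductions in Table 3 rest on different analysable numbers

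*Protocol article*

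**What the plan says.** The Interim analysis section plans one formal efficacy analysis of the maternal intervention, "to take place when half of the expected number of stillbirths and infant deaths have occurred". On the criterion it says: "This analysis will be run with an interim type I error of 0.007". A subordinate clause then translates that level into an effect size: "which is expected to require a maternal intervention relative efficacy of at least 13" per cent. It does not say which sample size, event rate or loss to follow-up lies behind that percentage. The next sentence says what the DSMB would do if this level was reached.

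Under Sample size and power, rates observed after the trial began "were used to update the sample size targets from 33 600 to 49 600 in the mother–infant cohort". The same paragraph says that at least 85% of enrolled participants were expected to have analysable endpoints. Table 3 lists detectable reductions for aim 1A at 80% and 90% power: 9.5% and 10.9% for the original design, 8.7% and 10.1% for the revised one. A footnote spells out the 15% loss for the original design only (28 560 of 33 600). The original rate is given as follows: "Original assumed composite baseline stillbirth and infant mortality was 105 deaths per 1000 births". The revised rate is 74 per 1000. The Study design section makes clear that the revised size is an enrolment figure: "We will enrol 49 600 pregnant participants".

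**The concern.** The interim percentage and the revised column of Table 3 describe the same comparison in the same trial, so one set of planning inputs should yield both. If it does not, two things are left open at the only efficacy look.

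The first is timing. Half the expected events is about 1,835 if everyone is analysable and about 1,560 if 15% are lost. The second of these is 43% of the information implied by Table 3 (1,560/3,670), not 50%.

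The second is reading the result. The phrase about the level being reached can be taken as the 0.007 level or as the 13%. For some observed effects the two give different answers.

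**Working it through.** **Inputs.** Original design: 28 560 analysable, 105/1000 (Table 3 and footnotes). Revised design: 49 600 enrolled, 74/1000 (Table 3); 85% of 49 600 is 42 160. The maternal comparison is 1:1 (two arms against two). Interim level 0.007. Its sidedness is not stated; it is taken as two-sided, z = 2.697.

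**Step 1: reproduce Table 3.** Two-proportion formula, two-sided 0.05, n = N/2 per group, p the control rate, q = p(1 − r), b = (p + q)/2. Solve for r:

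n = [1.96·√(2b(1−b)) + z_power·√(p(1−p) + q(1−q))]² / (p − q)²

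| Aim and basis | N | Rate | 80% / 90% power | Table 3 |
|---|---|---|---|---|
| 1A original, 15% loss | 28 560 | 105/1000 | 9.47% / 10.92% | 9.5% / 10.9% |
| 1A revised, no loss | 49 600 | 74/1000 | 8.72% / 10.05% | 8.7% / 10.1% |
| 1A revised, 15% loss | 42 160 | 74/1000 | 9.44% / 10.88% | no match |
| 1B revised, no loss | 49 600 | 9/1000 | 24.73% / 28.32% | 24.7% / 28.3% |
| 1B revised, 15% loss | 42 160 | 9/1000 | 26.67% / 30.52% | no match |
| 1B revised plus infant-only, no loss | 61 600 | 9/1000 | 22.34% / 25.61% | 22.3% / 25.6% |

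The original column allows for loss. The revised column matches full target sizes throughout.

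**Step 2: expected events, planning rate in both arms.**
- Revised, no loss: 49 600 × 0.074 = 3,670; half is 1,835.
- Revised, 15% loss: 42 160 × 0.074 = 3,120; half is 1,560.
- Original: 28 560 × 0.105 = 2,999; half is about 1,500.

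**Step 3: the reduction that just crosses 0.007 at half information.** Three forms:
- (a) fixed event count d: r = 1 − exp(−2 × 2.697/√d);
- (b) pooled two-proportion z with N/4 per arm, set equal to 2.697;
- (c) log hazard ratio, as in the planned Cox model, with treated-arm events reduced by the effect: √(E/4) × |ln(1 − r)| = 2.697, E = (N/4) × p × (2 − r).

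| Basis | (a) | (b) | (c) |
|---|---|---|---|
| Revised, no loss (49 600) | 11.8% | 11.8% | 12.2% |
| Revised, 15% loss (42 160) | 12.8% | 12.7% | 13.2% |
| Original (28 560) | 13.0% | 12.8% | 13.4% |

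No form on the Table 3 revised basis reaches 13%. Treating 74/1000 as a rate pooled over arms lowers that row to 11.4% to 11.8%, and a one-sided 0.007 lowers it further, so neither closes the gap.

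**Step 4: what the difference does.** At 1,835 events an observed 12.5% reduction gives z = (√1,835/2) × |ln 0.875| = 2.86, two-sided p = 0.004. That is past 0.007 but short of 13%. If the true reduction is 10.1%, the chance of crossing at the look is Φ((√d/2) × |ln 0.899| − 2.697): 34% at 1,835 events and 28% at 1,560.

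**The case against.** The strongest reply is that 13% is a sound rounding for the current design. With the only attrition figure the text gives for this cohort, 85% analysable, the revised size and rate yield 12.7% to 13.2%. The 11.8% to 12.2% needs zero loss, which the article nowhere states; it is inferred from Table 3. The error, if there is one, may lie in Table 3 and not in the interim section. The revised calculation is referred to a supplementary appendix table that is not shown. This stands as far as it goes: the percentage cannot be called wrong in itself. It does not remove the inconsistency, because the 85% that rescues the 13% is what Table 3's revised figures fail to match.

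A reader might go further and infer that the 13% was left over from the superseded design, since it inverts to 1,500 events, half of the original 2,999. That match depends on the form used. Allowing for fewer treated-arm events gives 13.4% for the original design and 13.2% for the revised one at 85%; the two-proportion form gives 12.8% and 12.7%. To the whole per cent the two cannot be told apart.

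A reader might also infer that the DSMB has been handed a wrong threshold. The article fixes the criterion as the 0.007 level and words the 13% as an expectation. Reaching the level leads the DSMB to consider all available data, not to an automatic stop. No charter is shown, so what the DSMB was given is unknown.

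**Conclusion.** The point holds in a narrow form. The 13% and the revised 8.7%/10.1% cannot come from the same analysable number. On Table 3's basis the boundary is about 12%; on an 85% basis it is about 13%, but Table 3's aim 1A entries would then be about 9.4%/10.9%. The documents do not show which place is off, nor that the 13% predates the revision.

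The size is about one percentage point on the boundary and about 275 events on the trigger (1,835 − 1,560). Type I error at the look is unaffected provided 0.007 is the rule applied. The result assumes a two-sided 0.007, 74/1000 as the control rate (which is how Table 3 reproduces), and half information at half the events. Severity is low.

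**What to change.** Choose one analysable number for the revised design, state it with its event rate and loss, and use it in both places:

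- **Keep Table 3.** Restate the interim look as about 1,835 composite events and about 12%, and say that the revised column assumes all 49 600 are analysable.
- **Keep 15% loss.** Leave the look at about 1,560 events and about 13%. Restate Table 3's revised aim 1A figures as about 9.4% and 10.9%, and recompute aim 1B on the same basis (about 26.7% and 30.5% for the mother–infant cohort; the combined figures need a stated loss for the infant-only cohort).

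In either case give the trigger as that event count, state the sidedness of the 0.007, and say that the 0.007 level governs and the percentage is only its approximate translation. The cost is a sentence in the interim section and, on the second route, some restated table entries. No participants or analyses are added.
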